### Intervention (a protocol for nurse-led care)

For this study, we summarised the guidelines of the Dutch College of General Practitioners and the care guideline for asthma in children, into one concise and easy-to-use protocol for practice nurses. This protocol encompasses an integral assessment of the patient, concerning: patient history, analyses of physical parameters, experienced complaints and restrictions, quality of life, investigation of the possible presence of allergy and determination of the expectations of the patient and their parents with regard to healthcare providers.

In addition, the protocol will contain education about asthma for the child and the parent, guidance on non-pharmacological interventions (eg, lifestyle advice, guidance on physical activity) and guidance on pharmacological interventions (eg, how, which and when different medication can/should be used). All this will lead to an individual care plan for the child. Furthermore, the protocol will contain guidance concerning diagnostic testing, treatment and follow-up. The participating practice nurses will receive up-to-date retraining in protocolled asthma care for children. When new or repeated medication is needed, the GP will approve the prescription.

### Follow-up visits in the intervention group (both randomised and non-randomised)

At baseline and at each control visit, asthma control will be determined by the practice nurse using a four-item questionnaire based on the Global Initiative for Asthma (GINA) guidelines.^17^

The content and frequency of follow-up visits will depend on the asthma control and medication use.

### Follow-up schedule for well-controlled patients in the intervention group

For well-controlled patients (based on GINA criteria) with asthma diagnosed in the previous year, control visits will be planned according to the medication used. For ‘as needed’ use of SABA, visits will be once in the first 3–6 months. When a patient is well controlled and with asthma diagnosis of >1 year, the control visit will be scheduled annually. When ICS dosage reduction in well-controlled patients is attempted (after 1 year of well-controlled asthma), control visits will be scheduled once every 3 months; at the lowest effective dose once every 3–6 months, and after 1 year, annually.

### Follow-up schedule for partly controlled/uncontrolled patients in the intervention group

Patients with partly or poorly controlled asthma (based on GINA criteria) who do not have optimal medication treatment, will receive additional medication according to the Dutch guideline (ie, add an ICS, or increase the dosage) and will be scheduled for control visits every 2–4 weeks until the asthma is well controlled or optimal medication treatment is reached. In the starting phase of ICS, control visits will be scheduled every 2–4 weeks. When the ICS is continued, review visits take place once in every 3 months in the first year. Children that remain uncontrolled or partly controlled with optimal medication treatment will be referred to secondary care. The referred children will still receive follow-up in the present study; the parents will be requested to continue filling out the electronic questionnaires and spirometry at t=18 months.

Figure 2 is a flowchart of the therapy and follow-up schedule by the practice nurse based on the guidelines of both the Dutch College of General Practitioners^6^ and the care guideline for asthma in children.^16^

**Figure 2 F2:**
[figure not shown]
Flowchart of the therapy and follow-up schedule by the practice nurse. ICS, inhaled corticosteroids; SABA, short-acting beta agonist.

### Follow-up schedule for the control group

The content and frequency of the control visits for the control group (‘usual care’) will be determined according to the discretion of the GP.

### Setting

The study will take place in academic and non-academic GP practices in the south-west region of the Netherlands. The academic network of GPs ‘PrimEUR’ in Rotterdam and the south-west of the Netherlands consists of 13 GP health centres with a total of 150 000 registered patients, including ±9000 children aged 6–12 years. This academic network aims to excel in training physicians to be GPs, to supervise medical students during their internships, to initiate healthcare innovation and to participate in research in primary care. Moreover, at least 14 (smaller) GP practices will be recruited to participate in the study. The number of participating GP practices can be enlarged by inviting more GPs to participate.

### Randomisation

The participating health centres (ie, one or more collaborating GP practices) will be the units of randomisation. They will be randomly assigned to either the intervention or control group (‘usual care’) with a 1:1 allocation as per a computer-generated stratified randomisation schedule. When a practice nurse works for several GP practices, all these practices will be part of the same cluster and randomised as one group. When a health centre consists of several GP practices with their own practice nurse, this health centre will also be considered as one cluster. When two practice nurses are working in one GP practice (not separated), this GP practice or health centre will be randomised as one cluster. When patients are eligible for inclusion in the trial and provide informed consent, a researcher will conduct the randomisation using an online randomisation programme and the patients will be informed in which treatment arm their GP practice is randomised. The cluster randomisation is conducted within 8 weeks after inclusion of the first patient of that GP practice into the present study. All subsequent patients of the same cluster will receive the same intervention.

Stratification will be based on the size of the GP practice and the number of years of experience of the GP. For example, GP practices in a single health centre (the same postal code) will be randomised in a stratified randomisation of four groups and, therefore, evenly distributed to the intervention and the control arm to minimise differences in baseline characteristics of the patients. A block randomisation with varying blocks (ie, 2–6 blocks) will be used to equally balance both groups. The sequence is kept secret from all researchers involved in the study.

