**Methods and analysis:**

The study will be a cluster-randomised open-label trial with an 18-month follow-up. Practice nurses will be the units of randomisation and children with asthma the units of analysis. It is planned to include 180 children aged 6–12 years. Primary outcome will be average asthma control during the 18-month follow-up measured by the Childhood Asthma Control Test (C-ACT). Secondary outcomes include C-ACT scores at t=3, t=6, t=12 and t=18 months; the frequency and severity of exacerbations; cost-effectiveness; quality of life; satisfaction with delivered care; forced expiratory volume in 1 s and forced expiratory flow at 75% and the association of high symptoms scores at baseline and baseline characteristics. Besides, we will conduct identical measurements in a non-randomised sample of children.

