The randomisation of the intervention (the practice nurse or group of practice nurses) will be conducted by stratified cluster randomisation. A pragmatic trial compares the effectiveness of an intervention in everyday practice with relatively unselected participants and under flexible conditions. Pragmatic trials have a high external validity due to the relatively unselected patients and are, therefore, helpful to answer the question whether the intervention has additional value in real practice.^43^ The aim of the current pragmatic trial is to compare protocolled nurse-led care by the practice nurse to the usual care of the GP. Cluster randomised trial designs are common in pragmatic research.^44–46^ Cluster randomised trials have particular utility in effectiveness and implementation studies. This design is appropriate for the evaluation of interventions that are naturally applied at cluster level, for example, general practices that opted for a certain stepped approach. Moreover, cluster randomisation avoids group contamination. Disadvantages of pragmatic cluster randomised trials are the generalisability and the recruitment bias; however, this can be (partly) solved by inviting all eligible patients from a cluster to participate in the trial. Another issue with cluster randomisation is the possible baseline imbalance between the randomised groups; however, this bias can be minimised by stratification of the clusters.

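### The Randomisation section gives two incompatible rules for a health centre with several practices: allocated whole as one cluster, or its practices spread over both arms

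*Protocol article*

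**What the plan says.** All of the conflicting text is in the protocol article, mostly in the Randomisation section.

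- **First paragraph, general rule:** "The participating health centres (ie, one or more collaborating GP practices) will be the units of randomisation".
- **First paragraph, a centre with several practices, each with its own nurse:** "this health centre will also be considered as one cluster". Practices that share a nurse are likewise joined into one cluster.
- **First paragraph, consequence:** "All subsequent patients of the same cluster will receive the same intervention".
- **Second paragraph, example given for the stratification:** "GP practices in a single health centre (the same postal code) will be randomised in a stratified randomisation of four groups", and these practices are therefore "evenly distributed to the intervention and the control arm to minimise differences in baseline characteristics of the patients".
- **Abstract, Methods and analysis:** "Practice nurses will be the units of randomisation and children with asthma the units of analysis". The Design section and the Discussion speak of a practice nurse or a group of practice nurses.
- **Discussion, among the reasons for the design:** "Moreover, cluster randomisation avoids group contamination".

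**The concern.** The two paragraphs deal with the same case, several practices within one health centre, and send it to different places. Under the first, every child in the centre enters the same arm. Under the second, children of one centre enter both arms. Whoever sets up the randomisation list cannot follow both.

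Three things depend on the answer:

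- **Which arm a child enters.** This cannot be undone once a cluster has been allocated and its parents informed.
- **Whether the comparison stays clean in those centres.** The Intervention section says that participating practice nurses are retrained and that the GP approves prescriptions. The control-group schedule leaves visits to the GP's discretion. In a split centre, nothing stated would stop a usual-care practice from taking up elements of the protocol from colleagues at the same address. That would pull the estimated difference towards zero.
- **What the cluster is.** The intracluster correlation of 0.04 in the sample size and the cluster level of the multilevel model must refer to the unit that was allocated. If a centre is split, it becomes a factor that crosses the arms and is no longer nested within one.

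**Working it through.** **1. The two rules side by side, for a centre with practices P1 and P2, each with its own nurse**

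| Step | First paragraph | Example in second paragraph |
|---|---|---|
| Unit drawn | the centre | each practice |
| P1 and P2 | always the same arm | shared out between the arms |
| Children of the centre | one intervention | both interventions |
| Relation of centre to arm | nested | crossed |

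No centre with two or more practices can satisfy both columns.

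**2. Does other text decide between them?** It does not. The rest of the first paragraph favours whole clusters. Other wording in the same section points to the practice: stratification uses the size of the GP practice and the GP's experience, patients learn the arm of their GP practice, and the eight-week deadline runs from the first patient of the practice. The study procedures for the cluster-randomised group start that deadline from the first patient of a cluster.

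**3. Does the sample size show which unit was meant?**

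Inputs: 126 children before adjustment, intracluster correlation 0.04, 15% loss and final total 180 (Sample size); 13 health centres and at least 14 smaller practices (Setting). The mean cluster size m is not stated.

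The 126 itself is not reproduced. The usual two-sided formula with a difference of 2, SD 4.1 and 80% power gives 66 per arm, 132 in total. That is a separate matter, and 126 is taken as given here.

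Design effect = 1 + (m − 1) × 0.04. Solving for m:

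- Loss as a multiplier of 1.15: 180 / 1.15 / 126 = 1.242, so m = 1 + 0.242 / 0.04 ≈ 7.1.
- Loss as division by 0.85: 180 × 0.85 / 126 = 1.214, so m = 1 + 0.214 / 0.04 ≈ 6.4.

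Assumption: the 13 centres and 14 practices each count as one cluster, giving 27. Then m = 180 / 27 = 6.67, and the design effect is 1 + 5.67 × 0.04 = 1.227. The total is 126 × 1.227 × 1.15 ≈ 178, or 126 × 1.227 / 0.85 ≈ 182.

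So 180 is compatible with centres kept whole. It is not proof, because the article does not state the cluster count used.

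**4. How far the unit moves the total (m varied, base 126)**

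| m | Design effect | × 1.15 | / 0.85 |
|---|---|---|---|
| 5 | 1.16 | 168 | 172 |
| 7 | 1.24 | 180 | 184 |
| 10 | 1.36 | 197 | 202 |

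The number of practices per centre is not given, so the value of m under splitting cannot be worked out.

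**5. Dilution under splitting.** If a share f of control children sits in split centres and they receive a fraction c of the effect, the expected difference is 2 × (1 − f × c). The article gives neither f nor c, so no figure follows.

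**The case against.** The best defence is that the first paragraph states whole-cluster allocation several times, while the splitting appears in one sentence introduced as an example. That sentence illustrates stratification by size and experience, and its four groups most naturally mean two-by-two strata. A single centre is unlikely to hold enough practices to fill four strata and balance each. The intended meaning may be only that clusters are balanced across arms. This is plausible as to intent, and it is a good reason to keep the first rule. It does not remove the conflict, because the sentence as written says that practices of one centre go to both arms. Nor is this a detail lost in condensing a full protocol: two stated rules conflict.

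Three stronger readings are tempting, and the article does not support them.

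- **A reader might infer that contamination is built into the design.** It arises only if the example is followed. If the first paragraph governs, no centre is split and this route does not exist.
- **A reader might put a size on it.** Suppose 10% to 30% of control children receive the full effect. The difference of 2 would then shrink to 1.8 to 1.4, and the required sample would grow by 1 / 0.9² = 1.23 to 1 / 0.7² = 2.04. The article gives no basis for such a rate, and the sum applies it to every control child. Only control children in split centres would be exposed, and a stand-alone practice, as some of the planned smaller ones may be, cannot be split.
- **A reader might count the practice nurse as a third, rival unit.** The Design section and the Discussion allow for groups of practice nurses, and the Randomisation section explains how nurses map to clusters. Only the abstract shortens this, so it needs alignment and is not a separate contradiction.

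**Conclusion.** The concern stands as an internal contradiction in the allocation rule. For a health centre with several practices, the two paragraphs of the Randomisation section prescribe different allocations, and nothing else in the article settles which applies. This needs correcting, because the rule decides which arm children enter and whether the contamination argument in the Discussion holds in those centres.

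The loss from contamination is conditional on the example being followed, and it cannot be quantified from the article. The implied cluster size of about 6.4 to 7.1 agrees with 27 whole clusters. That rests on the assumption that each listed centre and practice is one cluster, and on taking 126 as given.

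**What to change.** - Keep the first paragraph's rule: practices that share a nurse, or that belong to one health centre, form one cluster and are allocated whole to one arm.
- Delete or correct the example, so that the strata for size and experience apply between whole clusters and never within a centre. Postal code should not become a merging rule of its own; the article uses it only to describe a single centre.
- Bring the abstract's reference to practice nurses into line with this unit.
- Use the same unit for the design effect in the sample size and for the cluster level of the multilevel model.
- If any centre has already been split, report it and run a sensitivity analysis without it. The Discussion's statement on contamination then needs a qualification.

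The cost is a change of wording and one consistent cluster identifier in the database. The statistical downside is somewhat fewer and larger clusters than splitting would give, and so a higher design effect. If 27 whole clusters is what the plan already assumes, 180 largely allows for this. If clusters merge further because practices share a nurse, the mean size rises and the total should be rechecked: at 10 children per cluster it would be about 197 to 202.

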### Study procedures (cluster randomised group)

A researcher (nurse or medical student) will telephone the parents to check whether the children are eligible. Parents will receive the patient information letter with the informed consent form by regular post. When the patient and parents are willing to participate, the informed consent will be signed by the parents/legal guardians and sent to the department of General Practice by post. After all the parents of eligible children of one cluster (who are willing to participate) have provided informed consent, the randomisation is conducted by a researcher and the parents are informed (by telephone) in which treatment arm their child is allocated. Children who turn 12 years during the trial also have to give informed consent. The deadline for randomisation is 8 weeks after inclusion of the first patient of a cluster. Figure 3 is a flowchart of the study procedures.

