### Primary outcome measures

C-ACT scores will be analysed in a multilevel repeated measures regression model, which incorporates the C-ACT scores for all measurements, including the baseline measurement. This method takes into account within-patient correlation by modelling the covariance structures of the residuals per measurement. Several structures will be considered, starting with the unstructured covariance structure.

The differences in C-ACT scores between the two groups will be modelled by the interaction of treatment and measurement after baseline, assuming that any difference in C-ACT at baseline is due to chance. Additional variables will be considered for inclusion in the regression model if they are substantially different at baseline or if they are expected to be predictive of drop-out at a later stage.

Furthermore, a subgroup analysis will be conducted in which the total sample is divided into three groups according to their baseline characteristics; a group with insufficient asthma control (undertreated children), a group with sufficient asthma control and continuous ICS use (possible overtreated children) use and a group with the remaining children.

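### The protocol does not say whether a cluster closes to enrolment when it is randomised, and read naturally it lets families consent with the arm known

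*Protocol article*

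**What the plan says.** Two sections of the protocol article describe when a cluster is randomised.

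- **Study procedures (cluster randomised group):** "After all the parents of eligible children of one cluster (who are willing to participate) have provided informed consent, the randomisation is conducted". The same paragraph adds: "The deadline for randomisation is 8 weeks after inclusion of the first patient of a cluster".
- **Randomisation:** after eligibility and consent a researcher randomises, and "the patients will be informed in which treatment arm their GP practice is randomised". Then: "The cluster randomisation is conducted within 8 weeks after inclusion of the first patient of that GP practice into the present study". The next sentence is: "All subsequent patients of the same cluster will receive the same intervention".

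Three other places bear on the point.

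- The abstract (Methods and analysis) states: "The study will be a cluster-randomised open-label trial with an 18-month follow-up".
- In the Analyses part, the text on primary outcome measures models the treatment difference only after baseline, "assuming that any difference in C-ACT at baseline is due to chance". Further covariates are considered if they differ substantially at baseline or are expected to predict drop-out.
- The Discussion names recruitment bias as a disadvantage of the design and says that "this can be (partly) solved by inviting all eligible patients from a cluster to participate in the trial".

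**The concern.** If all willing families have consented before a cluster is randomised, there should be no later patients for a rule to cover. The Randomisation section nevertheless has such a rule, placed just after the arm has been allocated and disclosed. Consent forms travel by post, so week 8 can arrive before all are in. The protocol does not say what happens to a form that arrives afterwards.

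If it is accepted, the family, the practice and possibly the researcher who telephones know the arm when the family decides. Keeping the allocation sequence secret does not help here, because a late entrant takes an arm that is already disclosed. Families drawn by nurse-led care may differ in asthma control from families content with usual care. The arms would then differ at baseline through selection, while the primary model takes that difference to be chance. Baseline C-ACT also enters the average that defines the primary outcome.

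**Working it through.** **Step 1. Compare the two sections.**

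| Item | Randomisation | Study procedures |
|---|---|---|
| Consent before randomisation | Yes, for patients then eligible | Yes, for all willing families of the cluster |
| Latest time | 8 weeks from the first patient of the GP practice | 8 weeks from the first patient of the cluster |
| Patients after allocation | A rule that covers subsequent patients | None foreseen |
| Enrolment closes at randomisation | Not stated | Not stated |

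The deadline is common to both and is not itself a conflict. The conflict lies in the third row, and the fourth row leaves it open. One further difference is that a cluster can hold several practices, so a clock tied to the practice and one tied to the cluster need not start on the same day.

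**Step 2. What the primary model does with a selected group.** The plan gives no figure for this point, so there is none to reproduce. Inputs from the Sample size section are the minimally important difference of 2, the SD of 4.1 and 126 children (63 per arm) before inflation. The remaining inputs are assumptions:

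- f, the share of one arm enrolled with the arm known: 10%, 25% or 50%
- s, the lasting C-ACT shift of those children: 1 or 2 points
- rho, the correlation of baseline with follow-up C-ACT: 0.3, 0.5 or 0.7

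The arms then differ by f × s both at baseline and at follow-up. A model with a common baseline mean acts like adjustment for baseline and removes the fraction rho:

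bias = f × s − rho × f × s = f × s × (1 − rho)

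| rho | f 10%, s 1 | f 10%, s 2 | f 25%, s 1 | f 25%, s 2 | f 50%, s 1 | f 50%, s 2 |
|---|---|---|---|---|---|---|
| 0.3 | 0.07 | 0.14 | 0.175 | 0.35 | 0.35 | 0.70 |
| 0.5 | 0.05 | 0.10 | 0.125 | 0.25 | 0.25 | 0.50 |
| 0.7 | 0.03 | 0.06 | 0.075 | 0.15 | 0.15 | 0.30 |

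The range is 0.03 to 0.70 points, that is 0.03/2 = 1.5% to 0.70/2 = 35% of the minimally important difference. For the middle case, 0.25 × 2 × (1 − 0.5) = 0.25 points (12.5%). A simulation of that case with a baseline-adjusted model gave 0.249.

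**Step 3. Effect on the test.** Take 63 independent children per arm, one follow-up score and a two-sided 5% test:

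SE = 4.1 × √(2/63) × √(1 − rho²)

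With rho = 0.5 this is 0.730 × 0.866 = 0.63. A bias of 0.25 raises the type I error from 5% to about 6.8%. Over the whole grid it runs from about 5.0% to about 17%.

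**The case against.** The strongest reply is that the sentence on subsequent patients follows directly on a mention of the first included patient. It may mean those included after the first but still before randomisation. The two sections would then agree, and the Randomisation section does itself place consent before allocation. This reading is possible and the text does not exclude it. But the sentence comes after randomisation and disclosure, and no closure rule supports the milder reading. This part of the objection lowers confidence without removing the need for clarification.

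Several stronger conclusions might be inferred, and the documents do not support them.

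- **That late recruitment is planned, or has happened.** The text permits it on its natural reading and says no more.
- **That late entrants complete baseline C-ACT after allocation.** This would follow from their order of entry. The section on baseline measurements gives no order relative to randomisation, and the flowchart of study procedures is not shown.
- **That nothing in the plan could reveal the problem.** Baseline characteristics are summarised, and covariates that differ substantially may be added. These could hint at selection but could not attribute it to entry after allocation.
- **That the protocol overlooks recruitment bias.** It names the bias and claims only a partial remedy. Finding children by database search and inviting all of them limits selection at invitation, but not at consent.
- **That the primary analysis should be moved to children consented before randomisation.** This departs from the stated intention-to-treat principle and could be costly: 10-50% late entry across both arms would remove 18 to 90 of 180 children.

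It is also fair that the upper end of the bias range needs half of one arm to enter late and to differ by the full minimally important difference.

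**Conclusion.** The point holds as an unresolved inconsistency. One section has all willing families consent first, the other provides for subsequent patients after disclosure, and neither closes enrolment. On the natural reading this admits consent with the arm known in an open-label trial, which is at odds with treating baseline C-ACT differences as chance.

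The size and direction of any bias cannot be derived from the documents. The range of about 0.03 to 0.70 points rests wholly on the assumed share of late entrants, shift and correlation. Its lower end is negligible, and its upper end would matter for a trial designed around 2 points. The point should be fixed; confidence is moderate because the milder reading cannot be ruled out.

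**What to change.** 1. Delete the sentence on subsequent patients, or reword it so that it covers only children consented before their cluster was randomised.
2. State in both sections that trial enrolment of a cluster closes at its randomisation, when all consents are in or at week 8, and start the clock from the same event in both.
3. Require the baseline C-ACT to be completed before the arm is disclosed.
4. If children have already entered after allocation, flag them by consent date and report their number by arm. Keep the intention-to-treat analysis as primary and add a sensitivity analysis restricted to children consented before randomisation.

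The cost is a few sentences, one date flag and, if needed, one extra analysis. Some late responders would be lost. The Setting section already allows more practices to be invited, which can offset this. The clarification is worth making under either reading of the sentence.
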